### Outcome measures

**
*Primary outcome*
**

The difference of percentage of DPPC (PC32:0) in relation to total phosphatidylcholine composition (% of total PC in surfactant) at 48 hours between conservative and usual oxygen target groups.

**
*Secondary outcomes*
**

*1*. Surfactant index: This is a composite PC surfactant molecular index calculated from surfactant specific PC molecules (PC32:0, PC32:1 and PC30:0) and unsaturated surfactant PC34:1. This index will give a composite measure of surfactant PC alterations, which will provide a measure of surfactant PC status for the two different targets after 48 hours of oxygen therapy.
*This outcome is a measure of surfactant specific PC composition.*

     Surfactant index =

$\frac{\left\{PC32\text{:}0\text{+}PC32\text{:}1\text{+}PC30\text{:}0\right\}}{PC34\text{:}1}$

*2*. Surfactant phosphatidylcholine concentration (urea corrected) at 48 hours.
*This outcome is a measure of endogenous surfactant level.*

*3*. Systemic oxidative stress: Total free thiols, lipid peroxides and total surfactant oxidation products.
*This outcome will measure whole-body oxidative stress.*

**
*Secondary explanatory outcomes*
**

4. Surfactant total phosphatidylcholine and PC32:0
*methyl-*D
_9_choline enrichment at 48 hours.
*Measure of endogenous surfactant synthesis. This will measure the surfactant PC synthesis via the CDP-Choline pathway.*

*5*. Surfactant total lysoPC and lysoPC16:0 concentrations, composition and
*methyl*-D
_9_ choline enrichment at 48 hours.
*This outcome is a measure of endogenous surfactant breakdown. This will help to assess dynamic surfactant PC breakdown through hydrolysis.*

*6*. Surfactant oxidised PC composition and concentrations at 48 hours.
*Measure of endogenous surfactant breakdown. This will help to assess dynamic surfactant breakdown by oxidation.*

*7*. Whole-body redox balance by quantifying stable products of ROS (e.g., isoprostanes), RNS (e.g., nitrite, nitrate, nitrosation products) and RSS (e.g., total free thiols, thiosulfate, low molecular weight thiols including sulfide) at 48 hours from tracheal aspirates and plasma.
*Measure of lung and systemic redox status*.

**
*Secondary exploratory outcomes*
**

8. Exploratory outcomes: Comparison of clinical outcomes (ICU mortality, hospital mortality, 90-day mortality, ICU, and hospital length of stay) in relation to surfactant abnormalities.

9. Exploratory outcomes: Comparison of clinical outcomes (ICU mortality, hospital mortality, 90-day mortality, ICU, and hospital length of stay) in relation to specific markers of oxidative stress.

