### Pulmonary surfactant

Pulmonary surfactant is essential for the maintenance of alveolar integrity and consists primarily of phospholipids, of which 80–85% is phosphatidylcholine (PC), with dipalmitoyl-PC (DPPC) or PC32:0 accounting for 40–60% and proteins
^
10
^. Anionic phospholipids [such as phosphatidylglycerol (PG), phosphatidylinositol (PI), phosphatidylethanolamine (PE), and sphingomyelin] account for the remainder. DPPC (PC32:0) is the primary essential PC molecule required for the surface reduction property of surfactant. Surfactant is synthesised and secreted by alveolar type II (AT-II) cells. Surfactant deficiency from impaired synthesis/secretion, increased breakdown (either by hydrolysis or oxidation), or inactivation/inhibition by biophysical inhibitors can lead to compromised alveolar surface tension
^
11
^. In mechanically ventilated patients, surfactant deficiency can exacerbate the initial lung pathology and impair lung compliance, thus worsening the pre-existing systemic hypoxaemia
^
12
^.

Lungs are the primary target for direct oxygen toxicity, and animal studies have consistently demonstrated that lungs exposed to high oxygen concentrations exhibited quantitative and qualitative alterations in surfactant composition and function
^
13
^. In
*in-vivo* animal models, exposure to sub-lethal doses of oxygen results in decreased lung compliance, increased pulmonary leak, and inflammation with neutrophil migration. This is accompanied by hyaline membrane formation, alveolar septal oedema, fibrosis, and diffuse hyperplasia of alveolar epithelial cells
^
14
^. These changes mimic neonatal respiratory distress syndrome (nRDS) due to primary surfactant deficiency, implying that surfactant deficiency may contribute to acute hyperoxic lung injury.

Surfactant synthesis can be compromised due to hyperoxia. In isolated alveolar type-II cells, from rabbits exposed to hyperoxia, the surfactant phospholipid synthesis is compromised and there was a progressive development of acute lung injury
^
15
^. Moreover, exogenous surfactant replacement can significantly ameliorate hyperoxia-induced acute lung injury and improve alveolar phospholipid concentration
^
16
^. Besides the total surfactant pool size, hyperoxia can induce alterations in the surfactant composition with reductions in DPPC (PC32:0) and the PG/PI ratio, leading to compromised surfactant function
^
17
^. These
*in-vitro* and

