**Figure 4. f4:**
[figure not shown]
The incorporation of deuterated choline (
*methyl*-D
_9_ choline chloride) to quantify surfactant phosphatidylcholine (PC) synthesis via the CDP-choline pathway (
**A**) and the corresponding mass spectra for endogenous PC composition and newly synthesised PC fraction. ATP: adenosine triphosphate; CDP: cytidine diphosphate; CMP: cytidine monophosphate; CTP: cytidine triphosphate.

1. Does excess oxygen affect surfactant DPPC (PC32:0) synthesis and turnover?

A metabolic pathway for
*methyl*-D
_9_-choline incorporation into phospholipids is shown below, together with an example of the diagnostic mass spectrometry scans used for detection and quantification of unlabelled and deuterium-labelled PC.

We will aim to recruit patients and take the initial samples within 24 hours of randomisation into the UK-ROX study groups. The earliest time point will enable baseline assessment and subsequent 48 hours and 72 hours sampling times will assess the dynamic changes resulting from initiation of the intervention. The peak incorporation of
*methyl-*D
_9_ choline is between 48–72 hours after infusion, which will provide a measure of the maximal surfactant PC and LysoPC enrichment patterns monitoring both PC synthesis via the CDP choline pathway and the extent of enhanced breakdown through hydrolysis.

**
*Blood samples collection*
**

EDTA (10 ml) blood samples will be taken at baseline, 48, and 72 hours, (while hospitalised) after the
*methyl-*D
_9_-choline infusion. These samples will be taken only if the patient is still hospitalised. While in ICU, these samples are usually taken from pre-existing venous or arterial access lines. The collected blood samples will be stored at +4°C until transfer to the laboratory for processing. Processed samples taken at University Hospitals Plymouth will be transferred in frozen form to University Hospital Southampton for further analysis.

**
*Endotracheal tracheal aspirate*
**

Endotracheal aspirate (ETA) is a commonly performed procedure for secretion clearance in patients in the intensive care unit. Tracheal samples can be used to assess airway surfactant composition and metabolism. We have used tracheal aspirates to successfully isolate surfactant material in previous studies of healthy human volunteers and COVID-19 patients
^
26
^. Tracheal aspirate samples will be taken at 0, 48, and 72 hours, after the
*methyl-*D

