### Sample analysis

**
*Surfactant lipid composition and dynamic turnover*
**

Phospholipids, lysophospholipids and oxidised phospholipids molecular species will be analysed in tracheal fluid samples and from PExA. Mass spectrometric analysis of molecular species compositions of phosphatidylcholine (PC), phosphatidylglycerol (PG) and phosphatidylinositol (PI) in small volume ETA samples. Lysophosphatidylcholine products of PLA2-mediated hydrolysis of surfactant phospholipid will be determined by diagnostic precursor scans, together with molecular species compositions of intact surfactant phospholipid. Oxidation of unsaturated phospholipid initially generates higher mass peroxides, which then undergo chemical degradation to form truncated lower mass lipid aldehydes and hydroxyls. Intact and high and low mass oxidised phospholipids will be determined by specific MRM scans using electrospray ionization tandem mass spectrometry (ESI-MS/MS). An estimate of surfactant concentration will be determined by urea dilution analysis in parallel samples of bronchial fluid and plasma samples.

**
*Quantification of redox biology*
**

The extent of local and systemic oxidative stress with associated modifications of surfactant composition, alterations in cell signalling (due to interference with nitric oxide and hydrogen sulfide-related cell function) and shifts in redox status following the increased production of reactive oxygen species will be characterised in aliquots of pulmonary secretions and blood. Oxidative stress, nitric oxide, hydrogen sulfide and other redox related metabolites and products of ‘reactive species’ interactions will be quantified by an array of analytical platforms including ELISA, gas-phase chemiluminescence, HPLC, IC-MS, and LC-MS/MS to determine the following readouts: 8-isoprostanes, malondialdehyde (TBARS), nitrite, nitrate, total nitroso species, thiosulfate, sulfate, total free thiols, free and bound low-molecular weight thiols (including cysteine, homocysteine, glutathione), sulfide and polysulfide species according to local standard operating procedures.

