### Statistical analysis

The research hypothesis is that there is a difference in DPPC (PC32:0) fractional concentration between the conservative and usual oxygen groups. The primary endpoint is percentage DPPC (PC32:0) relative to total PC composition (% of total PC in surfactant) at 48 hours. For the primary analysis, we will use a multiple regression model adjusted for baseline to investigate the difference between the conservative and usual oxygen groups. If data are not normally distributed, we will investigate whether a log transformation improves normality. We will also perform an adjusted analysis to address clinical heterogeneity, using multiple regression, with up to 10 variables including the following baseline variables: age, gender, body mass index, percentage of PC32:0 in relation to total PC composition at admission, clinical conditions (e.g., sepsis, pneumonia) and concentration of inspired oxygen required at admission. We will also perform descriptive subgroup analysis for group differences and present them as box and whisker plots and scatter plots. As samples are collected from time points T=0, T=48 and T=72 hours as a secondary analysis, we will also investigate the use of mixed models to look at the difference between groups over time.

For the secondary outcomes of surfactant index; surfactant PC32:0, PC32:1, PC30:0; surfactant total phosphatidylcholine and PC32:0
*methyl-*D
_9_ choline enrichment; surfactant total lysoPC and lysoPC16:0 concentrations, composition and
*methyl*-D
_9_ choline enrichment and surfactant oxidised PC composition and concentrations (all measured at 48 hours), we will investigate the difference between groups using a two-sample t-test or Wilcoxon- Mann-Whitney test depending on the normality of data. If appropriate, adjusted analyses will also be performed as specified for the primary endpoint. The above will be repeated for the analysis of individual redox/oxidative stress markers listed above.

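### Outcome 5 counts lysoPC D9 enrichment towards surfactant breakdown, but that component carries PC synthesis with it and should be read only relative to its parent PC

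*Protocol article*

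**What the plan says.** In the protocol article, Outcome measures, item 5 covers "Surfactant total lysoPC and lysoPC16:0 concentrations, composition and" D9-choline enrichment at 48 hours. One interpretation is attached to the whole item: "This outcome is a measure of endogenous surfactant breakdown. This will help to assess dynamic surfactant PC breakdown through hydrolysis".

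Item 4, just above it, takes D9 enrichment of total PC and PC32:0 at the same time point and labels it "Measure of endogenous surfactant synthesis. This will measure the surfactant PC synthesis via the CDP-Choline pathway".

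The section on the methyl-D9 choline infusion (text after Figure 4) says that the 48-72 hour peak will give "maximal surfactant PC and LysoPC enrichment patterns monitoring both PC synthesis via the CDP choline pathway and the extent of enhanced breakdown through hydrolysis".

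Sample analysis states the chemical relation between the two: "Lysophosphatidylcholine products of PLA2-mediated hydrolysis of surfactant phospholipid will be determined by diagnostic precursor scans".

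Under Statistical analysis, the item 4 and item 5 variables stand in one list, and for all of them "we will investigate the difference between groups using a two-sample t-test or Wilcoxon- Mann-Whitney test depending on the normality of data". Adjusted analyses may follow where appropriate, as for the primary endpoint. The covariates named there are baseline variables, and PC enrichment at 48 hours is not among them.

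**The concern.** Enrichment is a labelled fraction, not an amount. Hydrolysis passes labelled and unlabelled molecules to lysoPC in the proportion in which they occur in PC. The labelled fraction of lysoPC therefore follows that of PC, which item 4 already uses as the synthesis measure. A two-group test of lysoPC enrichment that takes no account of PC enrichment picks up any synthesis difference and, under the stated interpretation, reports it as a difference in breakdown.

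The rationale makes such a difference plausible. The Pulmonary surfactant section says "Surfactant synthesis can be compromised due to hyperoxia", and it lists impaired synthesis and increased breakdown as separate routes to deficiency. Objective 1 sets out to quantify both. If synthesis falls in the arm with more oxygen, lysoPC enrichment falls there too. That would read as less hydrolysis in the arm where more breakdown is expected.

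**Working it through.** **The plan's own figures.** The article gives no kinetic rate and no expected value for item 5, so there is no figure to reproduce on this point. The sample size concerns the primary outcome only and does not enter.

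**Algebra.** Let P and L be the PC and lysoPC pools, e_P and e_L their labelled fractions, kh the hydrolysis rate constant, kc the lysoPC clearance, and b an inflow of unlabelled lysoPC from elsewhere.

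- dL/dt = kh·P + b - kc·L
- d(L·e_L)/dt = kh·P·e_P - kc·L·e_L
- With a steady lysoPC pool: de_L/dt = kc·(f·e_P - e_L), where f = kh·P/(kh·P + b)

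If b = 0, then f = 1 and kh drops out, so e_L follows e_P only. If b > 0, hydrolysis enters through f, but e_P still multiplies it.

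**Numerical check at 48 h.** All rates are assumptions:

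- PC pool 100 units, synthesis 1 unit/h, PC turnover 0.01/h, of which hydrolysis is 0.002/h
- lysoPC clearance 0.05, 0.2 or 1.0/h
- b either 0 or 0.2 units/h (equal to the baseline hydrolysis flux)
- choline enrichment rising over the 3 h infusion, then decaying with a time constant of 3, 8 or 15 h

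Pools may change after the perturbation. Entries are changes from baseline over all combinations.

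| Change | b | PC enrichment | lysoPC enrichment | lysoPC concentration | lysoPC/PC |
|---|---|---|---|---|---|
| Synthesis -30% | 0 | -21% | -21% to -24% | -7% to -11% | +0.2% to +5% |
| Synthesis -30% | 0.2 | -21% | -26% to -27% | -4% to -6% | +7% to +9% |
| Hydrolysis ×2 | 0 | -1% to +1% | -1% to +6% | +81% to +87% | +96% to +101% |
| Hydrolysis ×2 | 0.2 | -1% to +1% | +29% to +36% | +41% to +43% | +52% to +55% |
| Both | 0 | -20% to -22% | -20% to -22% | +64% to +67% | +101% to +104% |
| Both | 0.2 | -20% to -22% | -3% to +1% | +32% to +33% | +62% to +63% |

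**Hand checks.**

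- Synthesis cut: labelled PC scales by 0.7. The pool falls to 70 + 30·exp(-0.48) = 88.56, which is 0.8856 of baseline. So e_P changes by 0.7/0.8856 = 0.790, or -21%.
- Doubled hydrolysis with the other source, pool held fixed: f goes from 0.2/0.4 = 0.50 to 0.4/0.6 = 0.667, or +33%, inside the simulated +29% to +36%.

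**Reading.** With both changes and no other source, enrichment points the wrong way: 20-22% lower while hydrolysis has doubled. With the other source it shows almost nothing. LysoPC concentration and lysoPC/PC rise in both cases.

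**Enrichment ratio e_L/e_P.** It moves by -0.2% to -8% under the synthesis cut, so most of the synthesis effect is removed. Under doubled hydrolysis it moves by 0 to about +5% when b = 0, and by +30% to +36% when b = 0.2. It is not a hydrolysis rate.

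**The case against.** The strongest reply is that item 5 is a bundle. Its interpretive sentence covers concentration, composition and enrichment together and nowhere says that enrichment alone measures hydrolysis. Concentration does what is wanted, and item 4 is reported at the same time point, so a careful analyst would see a synthesis difference. The infusion section names PC and lysoPC enrichment patterns jointly, which can be read as product set against precursor. Derived ratios may also be defined in the full protocol or the SAP, neither of which is shown.

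Most of this stands, and it limits the point. Three stronger readings are tempting and not supported:

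- **That lysoPC enrichment says nothing about the amount hydrolysed.** This holds only if surfactant PC is the sole source of lysoPC, which the article does not state. With an equal unlabelled source, enrichment does respond.
- **That item 5 as a whole fails.** LysoPC concentration responds strongly to hydrolysis and shifts by only -4% to -11% under the synthesis cut.
- **That the infusion section equates unnormalised lysoPC enrichment with the extent of hydrolysis.** Its joint wording is ambiguous; it needs clarifying and is not plainly wrong. Nor is the absence of a ratio from an article a fault in itself.

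What the reply does not remove is the interpretation printed under item 5, with enrichment among its components, and a between-arm comparison that does not refer to parent PC. Adjustment as for the primary endpoint would not cure this, since the covariates named are baseline variables.

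**Conclusion.** The concern holds for the enrichment component of outcome 5 and no further. Unnormalised lysoPC D9 enrichment is confounded by PC synthesis, and the study's own rationale makes a synthesis difference between arms plausible. Under the assumed rates, a 30% synthesis cut alone lowers it by 21-27%. Combined with doubled hydrolysis, it ends 20-22% lower or roughly unchanged, so a real increase in breakdown could be reversed or hidden.

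The direction of the synthesis effect follows from lysoPC being formed from PC. The percentages rest on rates that the article does not give and should be taken as illustration. How much enrichment says about hydrolysis depends on whether lysoPC has another, unlabelled source, which the article leaves open.

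This is one component of one secondary explanatory outcome. The primary outcome, sample size and sampling schedule are unaffected. Severity: minor.

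**What to change.** - Let lysoPC16:0/PC32:0 and total lysoPC/total PC from the same sample, analysed on the log scale, carry the breakdown reading, alongside urea-corrected lysoPC concentration. Taking the ratio within one sample also cancels aspirate dilution.
- Report lysoPC enrichment only relative to parent PC enrichment in the same sample (for example lysoPC16:0 over PC32:0), as a descriptive measure and not as a hydrolysis rate.
- Reword outcome 5 so that unnormalised lysoPC enrichment is not presented as the extent of hydrolysis. Clarify in the infusion section that PC and lysoPC enrichment are to be read together.

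**Cost.** The ratios use quantities already planned for measurement, so no extra samples or patients are needed; one outcome is reworded and one sentence clarified. The downsides are that the ratios are skewed, hence the log scale, and that lysoPC/PC also depends on lysoPC clearance. A difference in clearance between arms would therefore still be mixed with hydrolysis, and the report should say so.

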### Sample size calculation

There is no previous index of surfactant damage documented in patients or animal models of acute hyperoxic lung injury. From ARDS and healthy volunteer studies, estimates of the mean (SD) for DPPC (PC32:0) composition are patients with ARDS 35.6% (SD 12.1%) and healthy controls 53.1% (SD 4.3%)
^
10,
24
^. Excess exposure will likely have alterations in DPPC composition from healthy volunteers but not significantly similar to the patients with ARDS, so we estimate that the standard deviation will be between 4.3 and 12.1 (
Table 1). With the higher estimate of SD, a sample size of 90 patients will achieve 90% power to detect a difference of 8.4% with a significance level of 0.05 using a two-sided two-sample t-test. Using the lower estimate, a sample size of 90 patients will achieve 90% power to detect a difference of 3.0% between groups with a significance level of 0.05 using a two-sided two-sample t-test. Allowing for an estimated 10% drop out we will recruit 100 patients.

**Table 1. T1:** Surfactant DPPC compositions a from healthy volunteers and ARDS patients used for the power calculations.

Variable	Timepoint	Group	Mean (SD)	Minimum absolute difference which can be detected at 90% power, N=90
DPPC or PC32: 0	48	ARDS	35.6 (12.1)	8.4
	48	Healthy control	53.1 (4.3)	3.0

### Statistical analysis

The research hypothesis is that there is a difference in DPPC (PC32:0) fractional concentration between the conservative and usual oxygen groups. The primary endpoint is percentage DPPC (PC32:0) relative to total PC composition (% of total PC in surfactant) at 48 hours. For the primary analysis, we will use a multiple regression model adjusted for baseline to investigate the difference between the conservative and usual oxygen groups. If data are not normally distributed, we will investigate whether a log transformation improves normality. We will also perform an adjusted analysis to address clinical heterogeneity, using multiple regression, with up to 10 variables including the following baseline variables: age, gender, body mass index, percentage of PC32:0 in relation to total PC composition at admission, clinical conditions (e.g., sepsis, pneumonia) and concentration of inspired oxygen required at admission. We will also perform descriptive subgroup analysis for group differences and present them as box and whisker plots and scatter plots. As samples are collected from time points T=0, T=48 and T=72 hours as a secondary analysis, we will also investigate the use of mixed models to look at the difference between groups over time.

For the secondary outcomes of surfactant index; surfactant PC32:0, PC32:1, PC30:0; surfactant total phosphatidylcholine and PC32:0
*methyl-*D
_9_ choline enrichment; surfactant total lysoPC and lysoPC16:0 concentrations, composition and
*methyl*-D
_9_ choline enrichment and surfactant oxidised PC composition and concentrations (all measured at 48 hours), we will investigate the difference between groups using a two-sample t-test or Wilcoxon- Mann-Whitney test depending on the normality of data. If appropriate, adjusted analyses will also be performed as specified for the primary endpoint. The above will be repeated for the analysis of individual redox/oxidative stress markers listed above.

For the exploratory clinical outcomes of ICU mortality, hospital mortality and all mortality censored at 90 days, we will use Cox regression with time-varying covariates to investigate the effect of surfactant abnormalities and specific markers of oxidative stress on survival. For ICU and hospital length of stay, we will use cause-specific Cox regression model to account for the fact that patients may die before being discharged. As an exploratory analysis, we will illustrate the relationship between surfactant markers and oxidative stress markers using scatter plots and will quantify these relationships using regression models.

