### Participants

All consecutive patients admitted will be screened according to the UK-ROX inclusion and exclusion criteria and they will be eligible if they fulfil the following criteria.

**
*Inclusion criteria*
**

•   Aged ≥ 18 years

•   Receiving invasive mechanical ventilation in the ICU for hypoxaemic respiratory failure

•   Receiving supplemental oxygen (fractional inspired concentration of oxygen (FiO
_2_>0.21 at the time of enrolment)

•   Anticipated to be mechanically ventilated for minimum of 72 hours

**
*Exclusion criteria*
**

•   Previously randomised into the UK-ROX in the last 90 days

•   Currently receiving extra-corporeal membrane oxygenation (ECMO)

•   The treating clinician considers that one UK-ROX trial intervention arm is either indicated or contraindicated

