### Data management

The clinical data collection will be enhanced within the ICNARC CMP research platform. Additional data collection will be obtained beyond the standard data collection by the UK-ROX clinical trial. The additional data will include baseline demographic variables, ventilation, and oxygenation parameters. The principal investigator will oversee and be responsible for data collection, quality, and recording. The nested CMP research platform enables data collection to be incorporated within the ICNARC routine CMP data collection process, streamlining data linkage. Study data will be made available online at the time study results dissemination.

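### The primary model adjusts for baseline DPPC alone; one prespecified pre-randomisation oxygenation covariate would bring a modest gain in precision and robustness

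*Protocol article*

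**What the plan says.** The Statistical analysis section of the protocol article gives the primary model: "we will use a multiple regression model adjusted for baseline to investigate the difference between the conservative and usual oxygen groups". The baseline variable is not named in that sentence. Baseline percentage DPPC is the natural reading, and no oxygenation or lung-injury variable is mentioned.

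The same section adds a second model: "We will also perform an adjusted analysis to address clinical heterogeneity, using multiple regression, with up to 10 variables". Its list includes age, gender, body mass index, "percentage of PC32:0 in relation to total PC composition at admission", and "clinical conditions (e.g., sepsis, pneumonia) and concentration of inspired oxygen required at admission". Mixed models over 0, 48 and 72 hours are to be investigated as a secondary analysis.

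Three other places bear on the point:

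- Participants, inclusion criteria: "Receiving invasive mechanical ventilation in the ICU for hypoxaemic respiratory failure", with any inspired oxygen fraction above 0.21 at enrolment.
- Data management: "The additional data will include baseline demographic variables, ventilation, and oxygenation parameters".
- Methyl-D9 choline infusion: the first samples are aimed for within 24 hours after UK-ROX randomisation.

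The Sample size calculation section takes its DPPC figures from "patients with ARDS 35.6% (SD 12.1%) and healthy controls 53.1% (SD 4.3" (percent), and states that "a sample size of 90 patients will achieve 90% power to detect a difference of 8.4% with a significance level of 0.05", using the higher SD and a two-sample t-test.

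**The concern.** Entry requires hypoxaemic respiratory failure with only a low floor on inspired oxygen, so severity of lung injury can vary widely between participants. The plan's own figures show that DPPC is lower in injured lungs. The only covariate in the primary model that carries this information is one blind-suction aspirate, with 20-50 ml instilled and an estimated 8-10 ml recovered. It is an imprecise marker of severity, and it may already reflect some hours of allocated oxygen therapy. An oxygenation ratio recorded before randomisation cannot be affected by allocation.

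Two things are at stake, both modest. The primary contrast may be less precise than the collected data allow. And severity may influence who is still alive and intubated to give an airway sample at 48 hours. If that loss also differs between arms, a regression on the available samples that omits severity would be somewhat biased.

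**Working it through.** **1. The plan's own figure.** Inputs from the Sample size calculation section: 90 analysed (45 per arm), two-sided 0.05, SD 12.1 or 4.3. With the noncentral t distribution, power is 0.903 for 8.4 points at SD 12.1 and 0.905 for 3.0 points at SD 4.3. The exact detectable differences at 90% power are 8.36 and 2.97. Recruitment is 90 / 0.9 = 100. The plan's figures reproduce, and they assume no gain from any covariate.

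**2. Precision from baseline DPPC alone.** The document gives no reliability or correlation, so these are assumptions. Let ρ be the reliability of one aspirate. If true DPPC is stable, the correlation between the baseline and 48-hour values is ρ, and the residual SD is 12.1 × √(1 − ρ²).

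**3. Adding severity.** Let c be the correlation of severity with true DPPC. Severity then correlates c√ρ with each measured value. The share of the remaining variance that it explains, which is also the share of sample size saved, is

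q = c²ρ(1 − ρ) / [(1 + ρ)(1 − c²ρ)].

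- ρ = 0.5, c = 0.8: q = 0.64 × 0.5 × 0.5 / (1.5 × 0.68) = 0.16 / 1.02 = 0.157.
- ρ = 0.7, c = 0.4: q = 0.16 × 0.7 × 0.3 / (1.7 × 0.888) = 0.0336 / 1.51 = 0.022.

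| ρ | Detectable difference, baseline DPPC only | Severity added, c = 0.4 | Severity added, c = 0.8 | q, c = 0.4 to 0.8 | Power at 8.4, baseline DPPC only |
|---|---|---|---|---|---|
| 0.3 | 7.98 | 7.87 | 7.45 | 2.7% to 12.8% | 0.927 |
| 0.5 | 7.24 | 7.14 | 6.65 | 2.9% to 15.7% | 0.964 |
| 0.7 | 5.97 | 5.91 | 5.53 | 2.2% to 14.3% | 0.995 |

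The gain is about 2-16% of the sample size. As the detectable difference scales with √(1 − q), that is about 1-8% of the detectable difference.

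**4. Loss of 48-hour samples.** Again the inputs are assumed.

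- Simulation with no true effect, SD 12.1, milder patients more likely to be unsampled, 10% unsampled in one arm and 20-30% in the other, and c = 0.5-0.7: the bias is about 0.15-0.7 points with baseline DPPC only, and under 0.1 with severity added.
- Hand check. Suppose half the patients are severe and all loss is among them. The severe share of those sampled is (0.5 − d) / (1 − d) for an arm that loses a fraction d. At 15% v 5% it is 0.35 / 0.85 = 0.412 against 0.45 / 0.95 = 0.474, a difference of 0.062. If the severity gap left after baseline adjustment is 4 points, the bias is 4 × 0.062 = 0.25; if it is 8.75 points, the bias is 0.54. At 10% v 10% the bias is 0 whatever the gap.

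For scale, the standard error of the contrast at ρ = 0.5 is 12.1 × √0.75 × √(2/45) = 2.2 points, so 0.7 points is about 0.3 standard errors.

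**The case against.** The strongest reply is that regression on the baseline value of the outcome, with a fuller adjusted analysis beside it, is a standard design and contains no false statement. In a randomised comparison, leaving out a prognostic factor does not itself bias the estimate. Clinical heterogeneity is addressed by the adjusted analysis, which lists six items within a limit of ten, diagnosis among them, so an oxygenation ratio could be added there without breaking the plan. Only patients expected to be ventilated for at least 72 hours are enrolled, and the plan expects 10% dropout overall. The larger precision gains need a severity-DPPC correlation of 0.8, which nothing in the document supports. All of this stands, and it keeps the point small.

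Three stronger readings are tempting and are not supported.

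- A reader might set the gap of 53.1 − 35.6 = 17.5 points against the 8.4-point detectable difference and infer an unadjusted effect twice as large. The 17.5 points compare ARDS patients with healthy volunteers. No participant here is healthy, and the gap is in DPPC itself, which the baseline covariate largely carries. The effect of severity that remains after baseline adjustment is not given.
- A reader might infer that the study is underpowered. The sample size took no credit for covariates, and baseline DPPC alone already raises power above 90% in the table.
- A reader might infer that dropout related to severity goes uncorrected throughout the plan. The adjusted analysis offers some correction, and the bias arises only if the loss also differs by arm.

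The reply does not dispose of one thing: a supplementary model leaves the primary estimate unchanged. Inspired oxygen alone also does not measure gas exchange without the PaO2 or SpO2 achieved, and diagnosis does not grade severity.

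**Conclusion.** The point holds as a modest, inexpensive improvement and not as an error. The primary model rests on one covariate, measured once with error and possibly after allocated treatment has begun, while a clearly pre-randomisation severity measure is left out. Under the assumed reliability and correlation, the omission costs about 2-16% of the sample size; towards the lower end it is negligible. The possible bias from selective loss of 48-hour samples is below about 0.7 points under the assumed patterns and zero if loss is equal across arms. A severity covariate would remove that bias only so far as loss depends on the measured severity, and not on the later clinical course.

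**What to change.** In the primary model, prespecify one continuous oxygenation covariate beside baseline DPPC: PaO2/FiO2, or SpO2/FiO2 where there is no blood gas, from the last values before UK-ROX randomisation. State in the same sentence that the baseline adjuster is percentage DPPC. Report the baseline-DPPC-only model as a sensitivity analysis. Carrying the same covariate into the secondary and mixed models would keep the analyses consistent.

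The cost is one degree of freedom, a sentence of text and a simple rule for missing values. The sponsor should also confirm that pre-randomisation values are in the collected dataset. The Data management section promises oxygenation parameters but names neither the ratio nor its timing, and participants join this sub-study after randomisation. The choice should be fixed before outcome data by arm are seen.
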